## Abstract

**Background:**

Selective serotonin reuptake inhibitors (SSRIs) are amongst the most prescribed antidepressants for adolescents with depressive symptoms and major depressive disorder. However, SSRIs have significant shortcomings as a first-line treatment considering that not all patients respond to these antidepressants. Amongst paediatric populations, meta-analyses indicate that up to approximately 40% of patients do not respond, and for those who do show benefit, there is substantial heterogeneity in response onset. The neurotransmitter serotonin (5-HT) plays a role in the clinical effectiveness and mechanisms of action of SSRIs. However, the exact and complete mechanism of action and reasons for the low response rate to SSRIs in some adolescent populations remains unknown.

**Methods:**

To examine SSRI response and the role of 5-HT, this study will employ a randomised double-blind within subject, repeated measures design, recruiting adolescent patients with major depressive disorder. Participants will be subjected to acute tryptophan depletion (ATD) and the balanced control condition on two separate study days within a first study phase (Phase A), and the order in which these conditions (ATD/balanced control condition) occur will be random. This phase will be followed by Phase B, where participants will receive open label pharmacological treatment as usual with the SSRI fluoxetine and followed-up over a 12-week period.

**Discussion:**

ATD is a neurodietary method typically used to investigate the impact of lowered brain 5-HT synthesis on mood and behaviour. The major hypothesis of this study is that ATD will be negatively associated with mood and cognitive functioning, therefore reflecting individual serotonergic sensitivity and related depressive symptoms. Additionally, we expect the aforementioned effects of ATD administration on mood to predict clinical improvement with regard to overall depressive symptomatology 12 weeks into SSRI treatment.

**Trial registration:**

Australian and New Zealand Clinical Trials Registry (ANZCTR) ACTRN12616001561471. Registered on 11 November 2016.

**Electronic supplementary material:**

The online version of this article (10.1186/s13063-018-2791-4) contains supplementary material, which is available to authorized users.

## Background

The Second Australian Child and Adolescent Survey of Mental Health and Wellbeing reported that approximately 5% of adolescents aged between 12 and 17 met criteria for a major depressive disorder (MDD) [1]. One of the most common pharmacological treatments for MDD in adolescents is the use of serotonin reuptake inhibitors (SSRIs). SSRIs are known to increase the availability of the neurotransmitter serotonin (5-HT) in the brain, and this is thought to contribute to the antidepressant effects of the pharmacological agent. However, it must be noted that the complete mechanism of action of SSRIs is not fully understood. The use of SSRIs is also associated with a number of limitations, including a delay in treatment response of often several weeks, as well as non-response for up to 40% in clinical populations of adolescents [2]. These limitations, when combined, place adolescents at an increased risk of experiencing a prolonged period in which symptoms of depression are not fully addressed or remain undertreated, particularly if the individual does not respond to SSRI treatment.

Therefore, there is a need to better understand the predictors of pharmacological SSRI treatment response to avoid treatment delays, and to enable adequate and personalised treatment options for young people with MDD. Examination of the predictors of SSRI treatment response requires a mechanistic understanding of the role of brain 5-HT in mood regulation [3]. Serotonin challenge procedures provide a research design that can clarify the mechanisms of brain 5-HT. An example of such a challenge methodology is acute tryptophan depletion (ATD). This methodology has been used in adults to investigate central nervous serotonergic neurotransmission, and additionally, the role of central nervous 5-HT in affective disorders [4–7].

ATD is a neurodietary method used to lower brain 5-HT synthesis, and works on the premise that the essential amino acid tryptophan (TRP) is the physiological precursor of brain 5-HT synthesis. As brain 5-HT can only be synthesised through the availability of TRP in the central nervous system, the consumption of foods or beverages lacking in TRP leads to a respective decline in central nervous 5-HT synthesis. ATD involves the administration of an amino acid mixture lacking in TRP after an overnight protein fast. The administered amino acids compete with endogenous TRP on the uptake into the central nervous system over the blood–brain barrier, which leads to decreased substrate availability for central nervous 5-HT synthesis for a period of several (usually 5–7) hours. Additionally, the administered amino acids stimulate protein synthesis in the liver, which takes TRP from plasma stores and also contributes to depletion (for a detailed review, see Dingerkus et al. [8]).

ATD has been shown to decrease mood in depressed adults in remission, particularly those using antidepressants, but not in healthy controls [9]. Mood response to ATD reliably predicted depressive episodes during a follow-up year [10]. Additionally, ATD reversed antidepressant-induced remission in a large proportion of a study sample involving adults with depressive symptoms [11]. Given its history of temporarily reversing remission amongst treated depressed adults, it may be that ATD is particularly potent amongst those who are responsive to SSRIs.

The impact of ATD on mood has only been investigated in adults, mostly because safe and effective ATD methods targeting central nervous 5-HT synthesis in young people were only recently demonstrated [12–14]. In order to make ATD suitable for use in young people, it must account for body weight. A body weight-adapted ATD procedure, called Moja-De, has been validated in rodents [15] and humans [8], but has never been used to investigate mood-related antidepressant treatment response in adolescents with MDD.

### Study objectives and hypotheses

The first objective of this study is to investigate the effects of ATD as a physiologically induced short-term central nervous serotonergic deficit on mood in adolescents with MDD (Phase A of the study) prior to open label treatment initiation with SSRI fluoxetine (Phase B of the study). We expect that, in Phase A, ATD will have dysfunctional effects on mood, emotional face recognition, aspects of reversal learning, and attention-related cognitive parameters as assessed within a testing battery, when compared to a balanced control condition. Such results would reflect a 5-HT sensitivity to ATD with regards to the aforementioned parameters relevant for depression [16, 17], and would be in line with the findings amongst the adult population [10, 18–20].

The second objective of this study is to determine if the effects of ATD on mood as a physiological 5-HT-related neurochemical and dietary challenge procedure predicts treatment response to SSRI administration after a period of 12 weeks of open label pharmacological treatment with fluoxetine (Phase B). We hypothesise that the effects of ATD administration on mood from Phase A will predict clinical improvement relating to depressive symptoms and overall depressive symptomatology 12 weeks into SSRI treatment (Phase B). Specifically, we hypothesise that ATD may be indicative of serotonergic vulnerability in relation to symptoms relevant for adolescent depression.

### Trial design

In Phase A, this study will use a randomised, double-blind, within subject repeated measures design. During this phase, participants will undertake the challenge procedures (either ATD or balanced control condition (BAL)) on two separate study days, spaced at a maximum of 7 days apart. In Phase B, this study will employ an open label fluoxetine treatment for a period of 12 weeks.

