#### Phase A

Phase A will consist of two separate study days, where participants will be randomised to either receive the ATD (i.e. an amino acid beverage lacking TRP) or BAL (which will consist of an ATD-based amino beverage plus TRP). Each study day will be separated by a maximum of 7 days. For each study day of Phase A, participants will be required to undertake a drug and pregnancy screen (if female), will be administered the respective amino acid challenge beverages (ATD and BAL), and a series of psychological and cognitive assessments (see below). A total of seven blood samples will also be taken per study day in phase A. The type of assessments and rationale for the blood samples are further described below in more detail.

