##### Amino acid challenge composition

The Moja-De ATD protocol (i.e. the ATD protocol that has been demonstrated to be safe for use in the child and adolescent population) employs amino acid administration within an aqueous suspension as a beverage, in which the relevant amino acid quantities are linked to the participant’s body weight. The amino acid quantities in ATD Moja-De are (dosage per 10 kg of body weight) as follows: L-phenylalanine (1.32 g), L-leucine (1.32 g), L-isoleucine (0.84 g), L-methionine (0.5 g), L-valine (0.96 g), L-threonine (0.6 g) and L-lysine (0.96 g). The respective control condition is known as the BAL condition. The BAL beverage contains the same amino acid quantities as described above for the ATD condition, but with an additional 0.7 g of TRP per 10 kg of body weight [23]. Research has shown that ATD is a safe and effective serotonergic challenge procedure [8, 15], and that it can be safely used in minors (Moja-De ATD test protocol) [12–14, 24].

Both the ATD and the BAL amino acid mixtures will be prepared by an approved manufacturing facility. The ATD amino acid beverage is made up of the seven dry amino acids as per the above calculations. Each subject receives a proportional amount of ATD amino acids within an aqueous suspension according to their body weight. For example, a 80 kg subject will receive 200 ml SyrSpend® SF (purified water modified food starch, sodium citrate, cinic acid, mali c acid, sodium benzoate, sulcralose, simethicone and cherry flavour) with the respective amino acids related to the individual’s body weight. As outlined above, the BAL beverage is made up of the same seven amino acids in the ATD with the addition of TRP (a total of eight amino acids) in the same way as the ATD beverage. Each subject receives a proportional amount of BAL amino acids within an aqueous suspension according to their body weight. Following the administration of both ATD/BAL beverages, apple juice will be offered following the mixture to wash out the taste.

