#### Trial management

This trial will be managed by the Centre & Discipline of Child and Adolescent Psychiatry, Psychosomatics and Psychotherapy and the Bentley Mental Health Service. The trial will employ several measures to ensure participant safety.

During Phase A, participants will consume the dietary protein amino acid serotonin depletion mixture (ATD challenge). This mixture may cause nausea and vomiting. Additionally, ATD is expected to decrease mood between 5 and 7 h (at maximum). To minimise associated risks with lowered mood, individuals with active suicidal ideation or plans will not be recruited to the study. A study doctor will be available at all times during Phase A to assess and manage these symptoms. Participants will be closely supervised and mood will be monitored frequently on the study days to identify those at risk. Mood will be formally assessed once per hour over 7 hours for each study day (Phase A). Tryptophan replacement (re-feeding) will be given at the end of each study day to normalise substrate availability for 5-HT synthesis. A thorough psychiatric assessment (i.e. mental state, risk assessment and management plan) will be conducted at the beginning and at the end of each study day to clear participants for discharge. The following day, participants will attend a clinical review by a study doctor to assess mood and risk. There will also be close monitoring in Phase B of the study, where participants will be reviewed by the study psychiatrists on a weekly basis for 12 weeks.

Any risk that emerges during the study (i.e. during Phase A or Phase B) will be managed by the research coordinator, who will liaise with the participant’s parent or guardian and arrange for prompt assessment by the participant’s study doctor or the nearest emergency department. All participants will have the research coordinator’s phone number, who will be available during working hours and after-hours of Phase A of the study, and during working hours of Phase B of the study. All participants will be given the Acute Response Team contact details for emergency after-hours support, which is an emergency community-based service that is available 24 h per day. The Acute Response Team will have been briefed about the rationale of this study and will also be regularly informed with regards to the number of participants involved at any point in time. Participants will be provided with a diary card with all relevant contact numbers.

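### The Phase A crossover sets a 7-day maximum but no minimum between challenge days, so tryptophan given on day 1 could alter the response to a depletion challenge on an adjacent day 2

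*Protocol article*

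**What the plan says.** The spacing rule appears twice in the Protocol article. Trial design places the two challenges "on two separate study days, spaced at a maximum of 7 days apart", and the Phase A section repeats: "Each study day will be separated by a maximum of 7 days". Neither place gives a lower bound, and none appears elsewhere in the article. By contrast, the Phase B section gives both bounds for the start of fluoxetine: 24 to 72 hours after the second challenge day.

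Other parts of the article bear on how close the two days can be:

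- **Fast.** Background describes the depletion drink as taken "after an overnight protein fast".
- **BAL drink.** Amino acid challenge composition says it matches the ATD drink but "with an additional 0.7 g of TRP per 10 kg of body weight".
- **Re-feeding.** Trial management: "Tryptophan replacement (re-feeding) will be given at the end of each study day to normalise substrate availability for 5-HT synthesis".
- **Review.** Trial management: "The following day, participants will attend a clinical review by a study doctor to assess mood and risk".
- **Duration.** Background says substrate availability falls "for a period of several (usually 5–7) hours". Trial management gives the same 5 to 7 hours as the longest expected period of lowered mood.
- **Order.** Blinding procedure and assignment of condition lists challenge order among the factors handled by the randomisation software.
- **Analysis.** Data preparation and statistical analysis names time and challenge as within-subject factors, and names no order or day term. It also plans to examine baseline amino acid levels, with ANCOVA if they matter.

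**The concern.** In a two-period crossover the minimum gap is what protects the treatment contrast, and it is the bound that is missing here. A site that follows the rule as written may book day 2 on the day after day 1. Re-feeding at the end of day 1 would then come shortly before the protein fast for day 2, and the clinical review would fall on the second challenge day. The article does not say how these steps fit together.

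The statistical question is whether day 1 changes day 2 differently in the two orders. Only BAL carries a tryptophan load in the drink, so a depletion on the day after BAL may start from a different tryptophan pool than a depletion on day 1. If that changes the response, two things are affected. The average ATD-minus-BAL contrast, which serves the first objective, is biased. Each participant's own ATD response, which the second objective uses to predict fluoxetine response, carries an error that depends on the order allocated. With 20 participants there is little room to absorb such an error.

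**Working it through.** **1. The plan's own figure.** The Power analysis section gives power 0.97 and critical F 3.26 for N = 20, effect size 0.4 and α = 0.05. Read the effect size as Cohen's f, and assume m = 3 measurements, k = 2 groups and correlation ρ = 0.5 (m, k and ρ are not stated). Then:

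- noncentrality = f²·N·m/(1 − ρ) = 0.16 × 20 × 3 / 0.5 = 19.2
- df = 2 and 36, critical F = 3.259, power = 0.972

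The stated figures reproduce. They do not depend on the gap between days, so they neither support nor weaken this point.

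**2. What an adjacent day 2 means in hours.** With the same start time on both days (assumed), the second drink follows the first by about 24 h. That is 24 − 7 = 17 h past the longest duration the article expects for depletion or lowered mood. On the article's figures the direct ATD effect is over by then. If an exponential decline is assumed instead, the share left at 24 h is 0.5^(24/h) for half-life h:

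| Assumed half-life | Share of ATD effect left at 24 h | Loss in average contrast (half the share) |
|---|---|---|
| 3.5 h | 0.9% | 0.4% |
| 7 h | 9.3% | 4.6% |
| 12 h | 25% | 12.5% |

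A 50% residue would need a 24 h half-life, which does not fit a 7 h maximum.

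**3. Which pathways survive balanced orders.** Let τ be the true ATD-minus-BAL effect, and let λ_ATD and λ_BAL be what each condition on day 1 adds to the day-2 result.

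- ATD first: expected difference = τ − λ_ATD
- BAL first: expected difference = τ + λ_BAL
- Average over balanced orders = τ + (λ_BAL − λ_ATD)/2

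Re-feeding follows both conditions. An additive effect is then equal in λ_ATD and λ_BAL and cancels. It matters only if it changes the size of the response to the day-2 challenge. The tryptophan in the BAL drink does not cancel, because ATD has no counterpart. For the article's example of an 80 kg subject it is 0.7 × 8 = 5.6 g.

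**4. Illustrative size of the remaining pathway.** Suppose prior loading weakens a day-2 ATD response by a share r, so that λ_BAL = −rτ and λ_ATD = 0. The average contrast becomes τ(1 − r/2). For the two-level contrast (m = 2, k = 2, ρ = 0.5), the noncentrality at r = 0 is 0.16 × 20 × 2 / 0.5 = 12.8; for other r, f is multiplied by (1 − r/2).

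| Assumed r | Average contrast | Power | Shift in each BAL-first participant's predictor |
|---|---|---|---|
| 0 | 100% of τ | 0.92 | none |
| 10% | 95% | 0.895 | 10% of τ |
| 25% | 87.5% | 0.84 | 25% of τ |
| 50% | 75% | 0.72 | 50% of τ |

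These values of r are assumptions. They also treat every participant as booked on adjacent days. The article gives no clearance data and no booking pattern, so the true r is unknown and may be near zero.

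**5. What an order or day term can do.** It removes a plain day effect and its contribution to the error. It cannot recover τ if the ATD response itself differs between day 1 and day 2, because with two orders that difference is confounded with order.

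**The case against.** The strongest reply is that the article already limits carry-over. Depletion and lowered mood are put at 5 to 7 hours, and re-feeding is given to restore substrate. The order is randomised, and baseline amino acid levels will be examined. The depression scales are completed at the start of each study day, so residual low mood on day 2 would be seen. This largely stands. A reader might infer from the missing minimum that induced low mood spills into day 2, or that re-feeding as such distorts the contrast. The documents support neither. The first runs against the stated duration, although that is an expectation and the article notes that the mood effect of ATD has been studied only in adults. The second is common to both orders and cancels if additive.

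It can also be said that the steps do not strictly contradict each other. Re-feeding can precede an overnight fast, and the psychiatric assessment at the start of a study day might double as the next-day review. That is fair: the article leaves the fit open, not impossible.

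Finally, this is a condensed account of a longer protocol whose timing figure is not shown, and a minimum may stand there. But the spacing rule is given twice with only an upper bound, while the Phase B start has both. As published, the rule allows adjacent days.

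The planned baseline ANCOVA helps only in part. It is conditional on a significant finding, and adjusting for a baseline level does not fully correct a response that differs by order.

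**Conclusion.** The point holds as a gap in the spacing rule with a possible, undemonstrated effect on the Phase A contrast. Consecutive challenge days are permitted, and the article does not say how they fit with re-feeding, the fast and the next-day review. The one clearly unequal pathway is prior tryptophan loading changing the response to ATD on day 2. Randomising the order would not remove that effect, and it would add order-dependent error to the individual predictor.

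Its size cannot be derived from the documents. The reductions to 95%, 87.5% and 75% of the true contrast, and the fall in power from 0.92 to between 0.895 and 0.72, rest on assumed values of r, on ρ = 0.5 and on adjacent days for everyone. They show how the bias scales and are not estimates. It would be wrong to read them as showing that the trial's result will be biased. The change is worth making because it is cheap and protects both objectives.

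**What to change.** 1. State a minimum interval next to the 7-day maximum, in Trial design and in Phase A, with its justification. Say how it fits with end-of-day re-feeding, the overnight protein fast and the next-day review. The length is for the sponsor to set.
2. Include challenge order and study day in the Phase A model; order is already handled in the randomisation.
3. Compare pre-challenge mood scores between day 1 and day 2 by order. The scales are already completed at the start of each study day. Do the same for tryptophan where a pre-drink sample exists. The article gives seven samples per study day but does not say that one precedes the drink on day 2, so this needs confirming.
4. Optionally, report the day-1-only ATD versus BAL comparison, which is free of carry-over, as a sensitivity result with its low power stated. With about 10 versus 10, and f = 0.4 read as d = 0.8, power is about 0.40 (two-sided t test, α = 0.05).

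The cost is one sentence in the schedule, a model term, one extra table and somewhat less booking freedom within the 7-day window. No extra visit is needed, and no extra blood sample if day 2 already has one before the drink.

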## Methods

### Setting of the study

The present study will be conducted at Bentley Health Service, Perth, Australia.

### Subjects and eligibility criteria

This pilot study aims to recruit *N* = 20 participants, and all participants who are referred to the study will be screened. Inclusion criteria for this study are as follows: adolescents aged between 12 and 17 years with a confirmed diagnosis of MDD (ICD-10 or DSM-5; diagnosis to be confirmed through the administration of the Kiddie Schedule for Affective Disorders and Schizophrenia (K-SADS) [21], as well as a full psychiatric assessment), no current suicidal ideation or suicidal plans, no other psychiatric co-medications at study entry, IQ > 85 (screened through the use of the Wechsler Abbreviated Scale of Intelligence (WASI-II) [22]), and no active or past eating disorder. Exclusion criteria include current abuse of alcohol and use of illicit substances, pregnancy in female participants, chronic medical or neurological disorders, subjects whose primary language is not English, treatment with other histaminergic or dopaminergic medications, disorders of amino acid metabolism, and contraindications against the use of fluoxetine. Participation in this study is entirely voluntary. Once recruited, participants will be able to withdraw their consent at any time by informing the study team.

